### Blood sample collection infant and mother (heel or finger stick)

For IgG testing using the X-map Luminex technology, a maximum of 2 mL infant cord blood is used. Furthermore, a maximum of 300 µl blood samples of the mother at birth and of the infants at 2 m of age is collected by heel or finger stick. Samples are tested for IgG antibody concentrations against pertussis antigens, diphtheria and tetanus. Antibody concentrations will be assessed in serum using a fluorescent bead-based multiplex immunoassay [23].

### Defining prematurity

We define preterm infants as infants born before 35^0^ w GA, although normally the cut-off for prematurity is set before 37^0^ w GA. We assume that for preterm infants born between 35^0^ and 36^0^ w GA second or third trimester maternal Tdap-vaccination will generally allow enough time for sufficient transfer of antibodies. We will use the same definition for term infants as used in the historical control group, i.e. ≥ 37^0^ w GA.

### Investigational product

Boostrix is a suspension for injection in a prefilled syringe containing diphtheria, tetanus and acellular pertussis vaccine (adsorbed, reduced antigen content). The Boostrix vaccine will be given as a single 0.5 mL intramuscular injection, in the deltoid muscle of the upper arm between 20^0^ and 24^0^ w GA. For subjects who are ill or have a moderate or high fever (rectal temperature of > 38.0 °C), vaccination will be postponed until the symptoms of illness and the fever have disappeared. Pregnant women in the historical cohort [24] received the same vaccine investigational product.

### Sample size calculation for immunogenicity part

To reach non-inferiority in term infants, the lower limit of the 95% confidence interval (CI) of the geometric mean concentration (GMC) after second trimester vaccination divided by the GMC after third trimester vaccination must be ≥ 0.5, with a one-sided 2.5% significance level and 80% power. As the GMC of anti-PT IgG in the historical control group (n = 58) was 26.1 IU/mL (95% CI 19.5–35.0), we need to include 53 term infants in the study. Taking into account 10% drop out or failed blood sampling, 58 term infants suffice.

Furthermore, non-inferiority in preterm infants is defined as 85% of infants with an anti-PT IgG above the 20 IU/mL at 2 m of age. This cut-off is used in many immunogenicity studies. With 10% precision, we need to include 49 blood samples from preterm mother-infant-pairs. Taking into account 10% drop-out or failed blood sampling, 54 preterm infants suffice. Due to the probability of multiple pregnancies in the preterm infant group and the likeliness of correlation between twins and triplets, preterm mother-infant-pairs are included and counted as one after multiple birth.

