**Methods:**

This prospective cohort study consists of two parts. In the acceptance part, pregnant women complete a questionnaire on determinants that underlie acceptance of a second trimester Tdap-vaccination, which is offered subsequently between 20^0^ and 24^0^ w of gestation. Vaccinated women complete an additional questionnaire on vaccination tolerability. Vaccinated women may also participate in the immunogenicity part, in which blood is drawn from mother at delivery and from infant at birth and 2 months after birth. Women are also eligible for the immunogenicity part if they received a Tdap-vaccination between 20^0^ and 24^0^ w of gestation via the national immunization program and get hospitalized for an imminent preterm delivery. Blood sampling continues until 60 term and 60 preterm mother-infant-pairs have been included. Pertussis-specific IgG antibody concentrations are determined in serum using a fluorescent bead-based multiplex immunoassay. For term infants, non-inferiority in IgG antibody concentrations against pertussis toxin (anti-PT) will be assessed referred to a historical control group in which mothers were Tdap-vaccinated between 30^0^ and 32^0^ w of gestation. For preterm infants, non-inferiority of anti-PT IgG concentrations is referred to as 85% of infants having ≥ 20 international units/mL at 2 months after birth.

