#### Primary objectives

##### Immunogenicity part

To evaluate non-inferiority of anti-Pertussis Toxin (PT) IgG antibodies in term infants at 2 m of age born of mothers who received a Tdap-vaccination between 20^0^ and 24^0^ w GA, compared to a reference anti-PT IgG at 2 m of age in a historical control group of term infants born of mothers who were vaccinated between 30^0^ and 32^0^ w GA in the period January 2014 to February 2016.To evaluate non-inferiority of anti-PT IgG in preterm infants at 2 m of age born of mothers who received a Tdap-vaccination between 20^0^ and 24^0^ w GA, as referred to at least 85% of preterm infants having anti-PT IgG concentrations ≥ 20 international units (IU)/mL as used in many immunogenicity studies.

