## Discussion

### General implications of results

This prospective cohort study will investigate the acceptance, tolerability and immunogenicity regarding maternal Tdap-vaccination between 20^0^ and 24^0^ w GA. Its results will provide valuable insights into anti-PT IgG antibody concentrations in term and preterm infants before primary infant vaccinations and how the vaccination schedule of these infants may be optimized in response to second trimester Tdap-vaccination. Determinants and beliefs that underlie pregnant women’s acceptance of second trimester Tdap-vaccination may guide antenatal care providers in the communication and recommendation of vaccinating early throughout gestation. Furthermore, assessing local reactions and solicited systemic adverse events following second trimester Tdap-vaccination will aid in communication about its safety profile.

Changes in the Dutch vaccination schedule may be considered if non-inferiority of anti-PT IgG antibodies in preterm infants at 2 m is addressed. Currently in the Netherlands, a Tdap-vaccination during pregnancy replaces the first infant vaccination for term infants who may then be vaccinated at 3, 5 and 11 m with a DTaP-IPV-Hib-HepB vaccine. Preterm infants are excluded from this reduced schedule and receive an extra vaccination at 2 m of age. GMCs of preterm infants at 2 m of age may inform us whether such a reduced schedule is also feasible for (late) preterm infants if they relate to GMCs at corresponding ages in term infants. For term infants, non-inferiority of anti-PT IgG antibody concentrations after second trimester Tdap-vaccination informs us that anti-PT IgG antibodies may still be higher at 2 m of age, compared to third trimester Tdap-vaccination. Since more than 93% of all annual births in the Netherlands are born after 37^0^ w GA [26], the results of this study may provide reassurance for pregnant women to obtain the maternal Tdap-vaccination at the earliest opportunity throughout gestation, i.e. at 22 w GA in the Netherlands.

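### The preterm primary criterion is a bare 85% with no confidence limit or error rate, so a passing result need not support a claim that at least 85% of preterm infants reach 20 IU/mL

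*Protocol article*

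**What the plan says.** The preterm criterion appears in three places in the protocol article.

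- Abstract, Methods: "non-inferiority of anti-PT IgG concentrations is referred to as 85% of infants having ≥ 20 international units/mL at 2 months after birth".
- Primary objectives, Immunogenicity part: "as referred to at least 85% of preterm infants having anti-PT IgG concentrations ≥ 20 international units (IU)/mL".
- Sample size calculation for immunogenicity part: "non-inferiority in preterm infants is defined as 85% of infants with an anti-PT IgG above the 20 IU/mL at 2 m of age".

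None of the three gives an interval, a significance level, a margin or a power. The sample size rests on precision: "With 10% precision, we need to include 49 blood samples from preterm mother-infant-pairs". It is then raised for losses: "Taking into account 10% drop-out or failed blood sampling, 54 preterm infants suffice". The abstract sets the recruitment target: "Blood sampling continues until 60 term and 60 preterm mother-infant-pairs have been included".

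The term criterion, in the same sample size section, is tied to "the lower limit of the 95% confidence interval (CI) of the geometric mean concentration (GMC) after second trimester vaccination divided by the GMC" in the third-trimester group. That limit must be at least 0.5, at one-sided 2.5% with 80% power.

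Under Statistical analyses, the immunogenicity part plans geometric means with intervals, t-tests and mother-to-infant ratios. It gives no interval or test for the preterm proportion.

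**The concern.** Two primary conclusions carry the label non-inferiority, but only the term conclusion has a stated error rate. A target of 49 for 10-point precision means that an observed 85% has a 95% interval reaching down to about 75%. Such a result would satisfy the preterm criterion as worded, yet would not show that at least 85% of preterm infants reach the cut-off.

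The conclusion has a use. The Discussion (General implications of results) says: "Changes in the Dutch vaccination schedule may be considered if non-inferiority of anti-PT IgG antibodies in preterm infants at 2 m is addressed". A reader there would reasonably take the preterm finding to be as firmly established as the term finding.

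**Working it through.** **Inputs.** Target 85%, precision 10 points, 49 pairs, 54 after losses (sample size section); 60 pairs (abstract). Multiple births count as one unit (sample size section), so independent binomial units are a reasonable model. The 95% level for the precision calculation is assumed, because it is not stated there.

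**1. The plan's own figure.** n = 1.96² × 0.85 × 0.15 / 0.10² = 48.98, rounded up to 49. Then 49 × 1.10 = 53.9, rounded up to 54. Both figures reproduce. The formula sizes an estimate; it sets no error rate or power for a success claim.

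**2. The rule as written.** Success is k/n ≥ 0.85, so k is at least 0.85n rounded up: 42/49, 46/54 or 51/60. The chance of success is the binomial tail P(X ≥ k | n, p).

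| True proportion | n = 49 | n = 54 | n = 60 | Range over n = 49 to 60 |
|---|---|---|---|---|
| 84% | 46.5% | 49.6% | 50.2% | 37-50% |
| 80% | 20.9% | 22.1% | 21.3% | 14-22% |
| 75% | 5.3% | 5.3% | 4.5% | 2-5% |

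The last column is wide because the cut-off moves in whole infants. At a true 80%, for example, the chance is 14.2% at n = 53 and 22.1% at n = 54.

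**3. What a just-passing result supports.** 42/49 = 85.7%, with an exact (Clopper-Pearson) 95% CI of 72.8% to 94.1%. The lower limits for 46/54 and 51/60 are 72.9% and 73.4%.

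**4. If the lower limit had to reach 85%.** The exact limit first reaches 85% at 47/49 or 57/60. The chance of success is then:

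| True proportion | n = 49 (47 needed) | n = 60 (57 needed) |
|---|---|---|
| 85% | 1.6% | 1.5% |
| 90% | 12.0% | 13.7% |
| 95% | 55.4% | 64.7% |

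The study was not sized for this rule.

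**5. If the floor were 75%.** This takes 85% minus the 10-point precision as a margin, which is an assumption. The exact lower limit first reaches 75% at 43/49 or 52/60. The chance of success is then:

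| True proportion | n = 49 (43 needed) | n = 60 (52 needed) |
|---|---|---|
| 75% (error) | 2.3% | 2.1% |
| 85% | 38.3% | 44.5% |
| 90% | 78.5% | 85.8% |

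**The case against.** The strongest reply is that the article never says the observed percentage alone decides. The 85% may be meant as a population target, with the interval and test left to a fuller document; planning for precision already presupposes an interval. This stands in part: the observed-proportion rule is a literal reading, not a quoted procedure. It does not dispose of the point. The article does not defer the preterm rule but defines it, and it found room for limit, significance level and power in the term rule beside it.

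A reader might also infer that the rule is a coin flip at its boundary, since it is met in 54% to 59% of trials at a true 85% with 49, 54 or 60 pairs. That reading fails. The primary objective asks for at least 85%, so success at exactly 85% is a correct conclusion. Any criterion on a point estimate passes about half the time at its threshold, and over all sizes from 49 to 60 the range is 45% to 59%. Nor is the term rule's 2.5% a like-for-like comparison: its boundary lies a full margin below equality, whereas 85% here is the target itself.

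A reader might further infer that 75% is the protocol's intended floor. The 10% is given only as precision. Under that reading the present rule would already err in at most about 5% of trials at a true 75%, and a simple Wald limit of at least 75% would give the same cut-offs: 42/49, 46/54 and 51/60. So it cannot be said that false success is wholly uncontrolled. What remains is that no floor is stated, and that excluding values below 75% is a weaker claim than at least 85%.

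Finally, the Discussion says only that schedule changes may be considered, and it also looks to how preterm geometric means relate to term ones. The 85% result is not the sole trigger.

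**Conclusion.** The concern holds in a limited form. The preterm primary criterion has no confidence limit and no error rate, unlike the term criterion beside it. Read literally, it would be met in 14-22% of trials at a true 80% and in 37-50% at a true 84%, for 49 to 60 evaluable pairs. A just-passing 42/49 leaves true values down to 72.8% open and cannot support a statement that at least 85% of preterm infants reach 20 IU/mL.

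These figures assume independent pairs and the literal observed-proportion reading. The arithmetic behind 49 and 54 is not in question, nor is the choice of 85% as a reference.

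**What to change.** Report the preterm proportion at or above 20 IU/mL with its exact two-sided 95% CI. Judge the criterion on the lower limit, against a floor that the sponsor fixes before analysis. Word the conclusion to match that limit, and claim at least 85% only if the lower limit itself reaches 85% (47/49 or 57/60).

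If the sponsor confirms that the 10-point precision was meant to imply a 75% floor, the criterion becomes 43/49 or 52/60. The conclusion would then be only that proportions below 75% are excluded.

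The enrolment target need not change. The cost is a less favourable claim and, with a 75% floor, one more infant needed to pass. At a true 85% the chance of meeting the criterion falls from 54.3% to 38.3% with 49 pairs, and from 58.8% to 44.5% with 60. At a true 90% it falls from 88.8% to 78.5%, and from 92.7% to 85.8%. An 85% floor would cost far more, with a 12-14% chance of success at a true 90% for 49 or 60 pairs, so floor and wording should be settled together.

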### Statistical analyses

#### Acceptance part

Items targeting social cognitive determinants and beliefs are measured on 7-point Likert scales. Items with the same underlying theoretical construct will be averaged into one single construct in case internal consistency is sufficient (Cronbach’s alpha α > 0.60 or Pearson correlation coefficient r > 0.50). Spearman’s correlation test will be used to explore univariate associations for attitude with social cognitive determinants, underlying beliefs and possible barriers and facilitators. We will control for the false discovery rate in multiple testing according to the Benjamini–Hochberg procedure. Next, variables with the largest predictive value for women’s attitude towards pertussis vaccination during pregnancy will be determined by random forest analysis. We will compare results with a similar study which assessed the determinants of acceptance of third trimester maternal vaccination, to distinguish determinants on the acceptance of maternal Tdap-vaccination in second versus third trimester of pregnancy [25].

#### Tolerability (extension of the acceptance part)

The percentage and 95% CI of pregnant women experiencing adverse events (AE) within 1 week after Tdap-vaccination are described by type and severity of the AE. Using binary generalized mixed models (GLMM), the association between the occurrence of symptoms in the week before and the week after vaccination will be analyzed. Proportions of absence from work and/or other activities, and medical intervention within 7 days after vaccination will be calculated together with 95% CI as well as the association of these items before and after vaccination using GLMM.

## Discussion

### General implications of results

This prospective cohort study will investigate the acceptance, tolerability and immunogenicity regarding maternal Tdap-vaccination between 20^0^ and 24^0^ w GA. Its results will provide valuable insights into anti-PT IgG antibody concentrations in term and preterm infants before primary infant vaccinations and how the vaccination schedule of these infants may be optimized in response to second trimester Tdap-vaccination. Determinants and beliefs that underlie pregnant women’s acceptance of second trimester Tdap-vaccination may guide antenatal care providers in the communication and recommendation of vaccinating early throughout gestation. Furthermore, assessing local reactions and solicited systemic adverse events following second trimester Tdap-vaccination will aid in communication about its safety profile.

Changes in the Dutch vaccination schedule may be considered if non-inferiority of anti-PT IgG antibodies in preterm infants at 2 m is addressed. Currently in the Netherlands, a Tdap-vaccination during pregnancy replaces the first infant vaccination for term infants who may then be vaccinated at 3, 5 and 11 m with a DTaP-IPV-Hib-HepB vaccine. Preterm infants are excluded from this reduced schedule and receive an extra vaccination at 2 m of age. GMCs of preterm infants at 2 m of age may inform us whether such a reduced schedule is also feasible for (late) preterm infants if they relate to GMCs at corresponding ages in term infants. For term infants, non-inferiority of anti-PT IgG antibody concentrations after second trimester Tdap-vaccination informs us that anti-PT IgG antibodies may still be higher at 2 m of age, compared to third trimester Tdap-vaccination. Since more than 93% of all annual births in the Netherlands are born after 37^0^ w GA [26], the results of this study may provide reassurance for pregnant women to obtain the maternal Tdap-vaccination at the earliest opportunity throughout gestation, i.e. at 22 w GA in the Netherlands.

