**Fig. 1 Fig1:**
[figure not shown]
Number of pertussis notifications per 100,000 per age category in 2005–2019 [31]

The Netherlands implemented several changes in the national immunization program in response to the increase. In 1999, the first pertussis containing vaccination was scheduled at 2 months (m) instead of 3 m. Late in 2001, an acellular pertussis component was added to the preschool diphtheria, tetanus and poliomyelitis booster dose at 4 years (y) of age and from 2005 onwards, the primary infant pertussis vaccinations also contained an acellular pertussis component instead of whole cell pertussis. However, surveillance data show that the incidence in young infants did not decrease following these changes (Fig. 1) [5]. In fact, an increase within this vulnerable age group was observed during every epidemic peak [2]. Adolescents and adults are likely a source of transmission to young infants [6].

In 2011, increased incidence rates of reported pertussis cases were followed by a large outbreak in 2012 in the Netherlands and surrounding countries, including England [7]. In response to an increasing number of pertussis related deaths, the English government decided to offer a maternal pertussis vaccination by means of a tetanus, diphtheria, acellular pertussis and poliomyelitis (Tdap-IPV) vaccine to all pregnant women during the third trimester. Maternal vaccination induces protection of young, not yet (fully) vaccinated infants. It confers passive immunity to the fetus by transplacental antibody transfer, which starts around 17 weeks (w) of gestational age (GA) and peaks in the third trimester [8]. After birth, maternal antibodies wane rapidly over time [9].

The uptake in England ranged around 70% and observational data showed a high vaccine effectiveness without any important safety concerns [9, 10]. To date, over 25 countries recommend maternal pertussis immunization with reassuring effectiveness and safety data. In December 2015, the Health Council of the Netherlands advised to offer a pertussis vaccination to all pregnant women in their third trimester [11]. In July 2018, the Ministry of Health, Welfare and Sports, decided to follow the advice of a maternal pertussis vaccination program. First vaccinations were offered mid December 2019.

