### Limitations

Assessing antibodies in term mother-infant-pairs based on a historical comparator results in performing analyses at different timepoints, which might affect pertussis antibody responses. However, the differences between these cohorts are limited to the time interval of Tdap-vaccination throughout gestation in both studies. Remaining study procedures, e.g. recruitment, data management and the used investigational product, are similar and performed by the same research institute and laboratory.

Since a maternal Tdap-vaccine could be obtained free of charge via study participation, pregnant women with high intention of acceptance may introduce selection bias due to high willingness of participation. After December 2019 when the vaccination is offered within the National Immunization Program for which no money is charged, women may still be likely to participate in this study for obtaining the vaccine from their antenatal care provider, instead of making an appointment for vaccination at a youth public healthcare service. Altogether, the results of second trimester Tdap-acceptance among pregnant women may be estimated more optimistic than in real life.

The results of our study are limited to a follow-up time of 2 m after birth. Maternal antibodies are known to interfere with term infants’ immune responses after primary vaccination series, which is known as blunting [24, 27–29]. The likeliness of a reduced immune response after primary vaccinations is not assessed in infants born of mothers who received second trimester maternal Tdap-vaccination and remains implicated for future research.

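### The 2-month preterm result is offered as informing a schedule whose first infant dose falls at 3 months, but nothing in the plan addresses antibody levels between 2 and 3 months

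*Protocol article*

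**What the plan says.** Protocol article, Discussion, General implications of results: "Changes in the Dutch vaccination schedule may be considered if non-inferiority of anti-PT IgG antibodies in preterm infants at 2 m is addressed". The same paragraph says that maternal vaccination currently "replaces the first infant vaccination for term infants who may then be vaccinated at 3, 5 and 11 m with a DTaP-IPV-Hib-HepB vaccine", and of preterm infants: "Preterm infants are excluded from this reduced schedule and receive an extra vaccination at 2 m of age". It then gives the link from data to schedule: "GMCs of preterm infants at 2 m of age may inform us whether such a reduced schedule is also feasible for (late) preterm infants", on condition that those values are in line with term GMCs at comparable ages.

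Sample size calculation for immunogenicity part: "non-inferiority in preterm infants is defined as 85% of infants with an anti-PT IgG above the 20 IU/mL at 2 m of age".

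On timing, Recruitment and follow-up puts the last infant sample at 2 months, before the first infant dose. The Background states that maternal antibody falls quickly after birth, without giving a rate.

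On decay, the secondary immunogenicity objectives include a comparison between term and preterm infants over the first 2 months. Statistical analyses, Immunogenicity part, gives a paired t-test of birth against 2-month GMCs for each group separately.

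Limitations: "The results of our study are limited to a follow-up time of 2 m after birth". The text that follows discusses only blunting of later vaccine responses.

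**The concern.** The evidence stops at 2 months, which is when preterm infants now receive a dose. On the reduced schedule they would have no infant dose until 3 months and would rely on residual maternal IgG in between. A result at 2 months does not by itself describe that month.

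The comparison with term infants could close the gap, because term infants already start at 3 months. It does so only if preterm antibody does not fall faster than term antibody after 2 months. Two paired tests, one per group, show that each group's concentration changed. They do not estimate or test whether the decay differs. The planned t-test between groups compares levels at a time point, not rates. The evidence most relevant to the third month is therefore promised as an objective but not produced by the stated analysis.

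At stake is what readers take from a primary endpoint. A result that just meets the 2-month criterion could be cited for the third month without any statement of what it implies there.

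**Working it through.** **Plan's own figure.** The preterm sample size reproduces: n = 1.96² × 0.85 × 0.15 / 0.10² = 48.98, so 49; with 10% added, 49 × 1.10 = 53.9, so 54. No stated figure is disputed.

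**Inputs.**
- Historical term controls at 2 months (Sample size calculation): n = 58, GMC 26.1 IU/mL, 95% CI 19.5-35.0.
- Preterm criterion (same section): 85% at 20 IU/mL.
- Assumed, because the documents give none: half-life 30, 40 or 50 days; first-order decay over 30.4 days; lognormal values; preterm spread equal to that of the historical term infants.

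**Spread.** SD(ln) = (ln 35.0 − ln 19.5) / (2 × t(0.975, 57)) × √58 = 0.5849 / (2 × 2.0025) × 7.616 = 1.11.

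**Preterm cohort exactly at the criterion.** Mean ln = ln 20 + 1.036 × 1.112, so GMC at 2 months = 63.3 IU/mL. One month's decay on the ln scale is d = ln 2 × 30.4 / half-life. The share at or above 20 IU/mL at 3 months is Φ(1.036 − d/1.112).

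**Historical term controls, same model.** Share at 2 months = Φ(ln(26.1/20)/1.112) = Φ(0.239) = 59%. At 3 months it is Φ((0.266 − d)/1.112).

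| Half-life (days) | d | Preterm share ≥ 20 at 3 m | Preterm GMC at 3 m | Term share ≥ 20 at 3 m | Term GMC at 3 m |
|---|---|---|---|---|---|
| 30 | 0.702 | 65.7% | 31.4 | 35% | 12.9 |
| 40 | 0.527 | 71.3% | 37.4 | 41% | 15.4 |
| 50 | 0.421 | 74.5% | 41.5 | 44% | 17.1 |

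With an assumed SD(ln) of 0.8 the preterm shares are 56.3%, 64.7% and 69.5%. With 1.3 they run from about 69% to 76%.

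**Why the decay comparison matters.** With equal decay, the preterm/term GMC ratio is the same at 3 months as at 2 months. With unequal decay it is multiplied by exp(−(d_preterm − d_term)). Suppose, purely as an example, half-lives of 30 days in preterm and 50 days in term infants: exp(−(0.702 − 0.421)) = 0.755. Equal GMCs at 2 months would then be a ratio of about 0.76 at 3 months.

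**What a projection from two samples can bear.** With samples at birth and 2 months, the projected ln value at 3 months is x₂ + 0.5(x₂ − x₀) = 1.5x₂ − 0.5x₀. Independent measurement error of variance v becomes (2.25 + 0.25)v = 2.5v. The projected mean is not biased by this, but the spread is inflated, which distorts a projected share above a cut-off.

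**The case against.** The strongest reply is that the schedule inference does not rest on the 85% criterion alone. The Discussion refers to term GMCs, and term infants already start at 3 months. On the model above, a preterm cohort exactly at 85% would be well above the historical term controls: GMC 63.3 against 26.1 IU/mL at 2 months, and 66-75% at or above 20 IU/mL at 3 months against 59% of those term infants at 2 months. The margin depends on the spread assumed; at SD(ln) 0.8 the preterm range of 56-70% straddles the 63% that the same model gives for term infants, Φ(0.266/0.8).

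This reply stands against a stronger reading that a reader might infer, namely that falling below 85% in the third month is a failure or leaves infants unprotected. The documents set no criterion at 3 months. They justify 20 IU/mL only by its common use in immunogenicity studies and do not present it as a protective threshold. Residual maternal antibody would also still be present.

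The reply does not remove the gap. The relative argument needs similar decay in both groups, and the stated analysis does not test that.

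It is also fair that the wording is tentative, that the objectives claim nothing beyond 2 months, and that the follow-up limit is stated. But the limit is not connected to the schedule inference, and the mismatch between the decay objective and its analysis is in the text itself. Lastly, two samples per infant cannot test log-linearity, and cord blood and heel or finger-stick samples differ in type. That restricts a projection to an exploratory role.

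**Conclusion.** The point holds in a limited form. The Discussion offers 2-month preterm results as informing a schedule that starts at 3 months, and nothing in the plan addresses the month between. The comparison with term infants, which could support that step, depends on a decay comparison that the secondary objectives promise and the analysis section does not deliver.

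The size is illustrative: from exactly 85% at 2 months to about 66-75% at 3 months, under lognormal values, SD(ln) 1.11 borrowed from term infants after third-trimester vaccination, and an assumed half-life of 30-50 days. The direction does not depend on the half-life, since any waning lowers the share. The amount does, and a cohort well above 85% at 2 months could still be at 85% at 3 months. Under the same assumptions that takes about 92-95% at 2 months (Φ(1.036 + d/1.112)).

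No objective, endpoint or sample size is wrong on this account. It is an inexpensive improvement to the analysis and a needed limit on interpretation.

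**What to change.** **Statistical analyses, Immunogenicity part.** Add a secondary, exploratory analysis:
- estimate each infant's log-linear decay rate from the cord and 2-month values, using actual sampling ages;
- compare the rates between term and preterm infants, with a 95% CI, which also delivers the stated secondary objective;
- report projected 3-month GMCs by group and the preterm/term ratio, with 95% CIs;
- give a projected percentage at or above 20 IU/mL only with a caveat about measurement error.

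State the assumptions: first-order decay continues to 3 months, and cord and capillary samples are comparable.

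**General implications of results, and Limitations.** State that the 2-month result alone does not describe antibody levels between 2 and 3 months. This limits what the result supports; no schedule or clinical rule is proposed.

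**Cost.** No new visits or blood: both samples are already taken. A 3-month sample would not help in preterm infants, because it would reflect the dose they now receive at 2 months. The work is one small extra analysis and a sentence in each of two places. The downside is reliance on a decay shape that two samples cannot check.
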